### Patient safety and monitoring of adverse events

The study is planned and conducted in consideration of Good Clinical Practice guidelines (ICH Topic E6, 2002) as well as in accordance with the medical professional codex and the Helsinki Declaration as updated in 2013. Serious risks for patients are not expected as GPs provide continuous medical care to all patients and the interventions under investigation are non-invasive. However, adverse events in terms of unexpected medical problems are monitored and discussed with the studies’ scientific advisory board. The occurrence of any serious adverse events must be reported by the GPs immediately, and decisions about continuation of the study protocol in these individual cases are made. Any decisions concerning the continuation of the whole study are to be made by the principal investigator.

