### Aims and objectives

Clinical effectiveness of primary health care for patients with PD/AG can potentially be improved by guiding patients to CBT-oriented exposure exercises within the framework of practice team-based case management. Focusing on CBT-oriented exposure exercises is clearly most promising in terms of clinical efficacy. It may further enhance feasibility from the viewpoint of practice teams, due to conceptual clarity. Case management procedures seem to be suitable to ensure the required safety of patients as the course of treatment is adequately monitored. If it can be shown that case management can effectively be delivered by health care assistants (HCAs), who are already members of the practice team, possibilities to increase the availability of evidence-based, low-threshold treatments for patients with PD/AG will arise.

The aim of this study is to test the clinical efficacy of a practice team-supported, self-managed exposure programme for patients with PD/AG in small general practices and to evaluate its cost-effectiveness. The study’s primary objective is to determine whether the programme is superior to usual care in terms of lower clinical severity of anxiety at follow-up six months after baseline. Secondary objectives are to determine if the programme is superior to usual care regarding further clinical parameters, patients’ perspectives on receipt of care, and direct and indirect health-economic costs from a societal perspective.

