CSSRI (modified version)	Health service use and productivity losses		•	•	•
Additional measures					
Screening questionnaire: OASIS; PHQ (panic module)	Patient-reported severity of anxiety symptoms and presence of diagnostic criteria for panic disorder	•			
Diagnostic interview (ICD-10-based checklist)	GP-reported diagnosis of panic disorder and agoraphobia	•			
Comorbid physical and mental disorders	GP-reported ICD-10 diagnoses	•			
Sociodemographic characteristics	Patient-reported age, sex, level of education, and marital status		•		
Treatment adherence questionnaire (self-developed)	Patient-reported adherence to self-managed exposure exercises			•	
GPs’ usual care	GP-reported referrals to psychiatric or psychological treatments (past six months)			•	•

Note. T0 = baseline before intervention; T1 = follow-up at six months; T2 = follow-up at twelve months; BAI = Beck Anxiety Inventory; CSSRI = Client Sociodemographic and Service Receipt Inventory; EQ-5D = EuroQol questionnaire; GP = general practitioner; MI = Mobility Inventory; OASIS = Overall Anxiety Severity and Impairment Scale; PACIC = Patient Assessment of Chronic Illness Care questionnaire; PAS = Panic and Agoraphobia Scale; PHQ = Patient Health Questionnaire. The treatment adherence questionnaire is not administered in the control group.

Patients’ anxiety symptoms and adherence to treatment are monitored by the HCA with the help of a newly developed monitoring checklist (Jena-Anxiety Monitoring List, JAMoL) during ten periodical, approximately biweekly telephone contacts. JAMoL results are reported to the GP. If symptoms worsen or adherence is suboptimal, the GP contacts the patient in order to check for necessary treatment adjustments (for example, changing planned exercises). In case of persistently severe anxiety symptoms or poor adherence to treatment, GPs are recommended to refer the patient to psychiatric or psychological outpatient treatments. However, as the intervention is applied in a real-world setting, GPs retain full clinical responsibility for patients. Therefore, during the whole course of the study, GPs may administer any medical treatments and referrals to any in- or outpatient treatments they deem to be useful.

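### The adverse event wording leaves out foreseen, non-serious worsening of anxiety, and the plan states no harm comparison made the same way in both arms, although the BAI data already collected would allow one

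*Protocol article*

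**What the plan says.** All references are to the protocol article.

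- **Patient safety and monitoring of adverse events.** The rule for adverse events in general is that "adverse events in terms of unexpected medical problems are monitored", and they are taken to the scientific advisory board. Serious events have a separate sentence without that limit: "The occurrence of any serious adverse events must be reported by the GPs immediately".
- **Interventions pertaining to the individual participants.** Worsening in the intervention arm is foreseen: "If symptoms worsen or adherence is suboptimal, the GP contacts the patient in order to check for necessary treatment adjustments". It is picked up with a checklist (JAMoL) that the health care assistant completes "during ten periodical, approximately biweekly telephone contacts. JAMoL results are reported to the GP". The control arm receives usual care, and no counterpart to the checklist calls is described for it.
- **Table 1.** BAI is collected at T0, T1 and T2. The table note withholds only the adherence questionnaire from the control group.
- **Statistical analyses.** BAI at T1 is analysed as a total score in a mixed linear model. No count of patients who worsened is mentioned.
- **Aims and objectives.** As part of the rationale: "Case management procedures seem to be suitable to ensure the required safety of patients".

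**The concern.** The most foreseeable harm of an exposure programme is that anxiety or avoidance becomes worse. The protocol expects this to happen in some patients and provides a response to it. If a GP applies the adverse event wording as written, a non-serious worsening that the programme anticipates is not an unexpected medical problem and need not be recorded as an adverse event.

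The wording may also act differently in the two arms. The trial is not blinded, and only intervention teams are trained in the exposure rationale and in checklist monitoring. A GP with that training has more reason to regard a rise in anxiety as expected. On the other hand, only intervention patients have scheduled programme contacts at which worsening is looked for. These two influences pull in opposite directions, so counts of worsening from contacts or checklists would not be comparable between arms.

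The study asks whether practice teams without extensive mental health training can deliver exposure. A report of better mean BAI and few adverse events would leave open whether some patients did worse under the programme.

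**Working it through.** **1. The passages side by side.** The safety section limits monitored adverse events to unexpected problems. The intervention section names worsening symptoms as a foreseen occurrence and routes it to the GP for treatment adjustment. No link from that route to adverse event reporting is stated. A foreseen, non-serious worsening therefore falls outside the literal adverse event wording. A worsening that meets the definition of serious falls inside, because the serious-event sentence covers any such event.

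**2. Scheduled programme contacts.** Intervention arm: 4 GP appointments + 10 assistant calls = 14. Control arm: none described, although these patients do see their GP under usual care. The figure shows that detection is unequal. It is not a count of all contacts.

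**3. The protocol's own figures used below.** From Sample size: SD 11, intra-cluster correlation 0.07, six patients per practice, dropout about 20%, 37 practices per arm.
- Planned effect: 0.35 × 11 = 3.85 points, as stated.
- Design effect: 1 + (6 − 1) × 0.07 = 1.35, as stated.
- Patients per arm: 37 × 6 = 222, as stated.

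**4. A mean benefit can coexist with a harmed minority.** Suppose, for illustration only, that 10% of intervention patients end 10 points worse than they would have under control and 90% end 5.4 points better. The mean benefit is 0.9 × 5.4 − 0.1 × 10 = 4.86 − 1.00 = 3.86 points, which matches the planned 3.85. About 0.10 × 222 = 22 patients per arm would be worse off, and the stated analysis of mean BAI would show success.

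**5. Threshold for reliable deterioration.** Formula: 1.96 × SD × √(2(1 − r)), with SD = 11. The reliability r is not in the document and is assumed.

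| r (assumed) | Calculation | Rise in BAI |
|---|---|---|
| 0.85 | 1.96 × 11 × √0.30 | 11.8 |
| 0.90 | 1.96 × 11 × √0.20 | 9.6 |
| 0.95 | 1.96 × 11 × √0.10 | 6.8 |

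BAI is a whole-number score, so r = 0.90 gives an increase of at least 10 points. On the 0–63 scale, a patient with a baseline above 63 − 10 = 53 cannot meet that threshold.

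**6. Precision of a between-arm comparison.** Followed per arm: 222 × 0.8 = 177.6. Effective number per arm, assuming the 1.35 also applies to a binary outcome: 177.6 / 1.35 = 131.6. The 95% half-width for a difference, at a common rate p, is 1.96 × √(2p(1 − p)/131.6).
- p = 0.05: 1.96 × √(0.095/131.6) = 0.053
- p = 0.10: 1.96 × √(0.18/131.6) = 0.072

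The interval is therefore about ±5 to ±7 percentage points. The rates are assumed.

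**The case against.** The strongest reply is that this is a journal article giving adverse events little space, that it cites Good Clinical Practice, and that working definitions and a deterioration endpoint commonly sit in the full protocol or the analysis plan. This stands for anything merely absent, so the missing deterioration table is not in itself an error. It does not dispose of the point, because the article states a limiting rule; if a fuller document defines adverse events more widely, the sentence still needs to be brought into line.

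Four stronger readings are tempting, and the documents do not support them.
- *A reader might infer that worsening anxiety is explicitly excluded or that serious deterioration would go unreported.* The exclusion is an inference from one word, and any serious adverse event must be reported.
- *A reader might describe the exposure as unsupervised.* It is self-managed, but with four GP appointments, GP supervision of progress, ten calls, and GP contact if symptoms worsen.
- *A reader might think that worsening is recorded only on the checklist.* BAI, avoidance, panic attacks, depression and quality of life are collected in both arms at all three times, as far as possible also from patients who discontinue.
- *A reader might conclude that the trial has no between-arm comparison of harm.* Average harm would show in the primary and secondary analyses. What is not described is a comparison of how many patients worsened.

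It is also fair to say that control patients are not without contact (the protocol states that GPs provide continuous care to all patients), that the safety remark in the aims is tentative rationale and not an objective, and that removing *unexpected* alone would add events detected more readily in the intervention arm. The last objection shapes the fix.

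**Conclusion.** The point holds in a limited form and should be addressed. The stated wording, taken literally, omits foreseen non-serious worsening. Active monitoring for it is described in one arm only, and the stated BAI analysis cannot show a minority who deteriorate. The data needed for a symmetric measure are already planned in both arms.

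The size of any actual harm is unknown, and the 10% in the illustration is not a forecast. The conclusion about the wording rests on the text alone. The 10-point threshold rests on an assumed reliability of 0.90 and on the SD of 11 from an earlier primary care sample applying to this population. The precision figures rest on assumed rates of 5 to 10% and on the planning design effect and dropout.

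**What to change.** 1. In the safety section, remove *unexpected* as the limit on adverse events.
2. Add an exploratory harm outcome: the proportion of patients with reliable BAI deterioration from T0 to T1 and from T0 to T2, for example an increase of at least 10 points, with the assumed reliability stated. Compare the arms with a model that accounts for practice and give a 95% confidence interval.
3. Treat checklist worsening, and adverse events found through programme contacts, as descriptive within the intervention arm. Without this, step 1 would increase the imbalance in detection.
4. Report dropouts and cancellations by arm beside the result. Under Confidentiality of data, the data of patients who cancel are deleted unless they agree to further use, so some who left because they worsened may not be counted.

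The cost is a short change of text and one extra table, with no new data or visits. The limitations are low precision, no view of transient worsening between assessments, possible loss of patients who leave, and less room to worsen for patients with a high baseline BAI.

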### Research ethics approval

The enrolment of patients did not start unless there was a written and unrestricted positive vote of the local ethics committee. The ethics committee of the Friedrich-Schiller-University at the Medical Faculty (Jena, Germany) approved the study protocol on 17 August 2012 (Approval number 3484-06/12). Protocol modifications are communicated to the ethics committee by amendment.

### Informed consent

Eligible patients are fully informed about the study by their GP and a written patient information sheet is handed out to them prior to their participation. This ensures that patients’ decision about participation is based on knowledge about: anxiety diagnoses and evidence-based therapeutic options; purpose, content, and conduct of the study; potential benefits and risks for their health; data management procedures; and voluntariness of participation. In case of acceptance, patients have to sign an informed consent sheet to be included.^a^ Participants may cancel their participation at any time, without disclosing reasons for their cancellation and without any negative consequences regarding their future medical care.

### Confidentiality of data

All personal information obtained about patients and general practices during the recruitment process (for example, names, addresses, contact details) are held in accordance to the German Federal Data Security Law (BDSG) and medical confidentiality rules. To secure confidentiality, these data are stored in a password-protected server of Jena University Hospital. Paper-based personal information is stored in a locked filing cabinet located at the research office. Access to any personal data is strictly restricted to the project team. Personal information is never passed to any third parties.

Research numbers are assigned to general practices and patients at the time of inclusion. Any clinical data (as obtained by CRFs or other report forms) are encrypted by these research numbers. Clinical data are held strictly apart from personal data and stored on a central server of Jena University Hospital. Encrypted clinical data may be passed to project partners for analysis purposes. In case of individual study cancellations, personal and clinical data are extinguished except that patients explicitly affirm further use.

## Trial status

The trial is ongoing as the project team is still recruiting general practices and patients.

### Endnote

^a^Patient information sheet and informed consent form can be obtained from the authors upon request.

## Abbreviations

BAI: Beck Anxiety Inventory; BDSG: German Federal Data Security Law; CBT: cognitive behavioural therapy; CCM: collaborative chronic care models; CRF: case report form; CSSRI: Client Sociodemographic and Service Receipt Inventory; EQ-5D: EuroQol questionnaire; GP: general practitioner; HCA: health care assistant; ICD-10: *International Classification of Diseases, version 10*; ICER: incremental cost-effectiveness ratio, ICH, International Conference on Harmonisation; MI: Mobility Inventory; OASIS: Overall Anxiety Severity and Impairment Scale; PACIC: Patient Assessment of Chronic Illness Care questionnaire; PAS: Panic and Agoraphobia Scale; PHQ: Patient Health Questionnaire; PD: panic disorder; PD/AG: panic disorder with or without agoraphobia; QALYs: quality adjusted life years.
